## Amendments

| Amendment | Date                                                                                                                              | Summary of changes                                                                                                                                                                                                                                                                                                                                                 | Reason                                                                              |
|-----------|-----------------------------------------------------------------------------------------------------------------------------------|--------------------------------------------------------------------------------------------------------------------------------------------------------------------------------------------------------------------------------------------------------------------------------------------------------------------------------------------------------------------|-------------------------------------------------------------------------------------|
| 1         | 1 September 2022

This amendment was approved after unblinding but before conducting the affected subgroup analyses. | Section 4.3.3.3:
".. participants' "pandemic status" is classified into three categories based on the timing of randomisation and completion or withdrawal: (1) reached primary endpoint at week 13 or dropped out before pandemic onset; (2) randomised and on study not yet reached primary endpoint at pandemic onset; (3) randomised after pandemic onset." | Avoid using post-randomisation information (date of withdrawal) to define subgroups |
|           |                                                                                                                                   | Section 4.3.3.5:
Childhood ADHD status (baseline WURS score $\geq 36$ 46)                                                                                                                                                                                                                                                                                       | Correct typo                                                                        |

**List of abbreviations**

| Abbreviation | Definition                                   |
|---------------------|-----------------------------------------------------|
| AE                  | Adverse Event                                       |
| AWQ                 | Amphetamine Withdrawal Questionnaire                |
| BPRS                | Brief Psychiatric Rating Scale                      |
| CBT                 | Cognitive Behavioural Therapy                       |
| DASS                | Depression & Anxiety Survey Scale                   |
| DEQ-5               | Drug Evaluation Questionnaire                       |
| ESSI                | ENRICHD Social Support Inventor                     |
| ISI                 | Insomnia Severity Index                             |
| ITT                 | Intention-to-treat                                  |
| LDX                 | Lisdexamfetamine                                    |
| MAR                 | Missing at random                                   |
| MMRM                | Mixed model for repeated measures                   |
| MNAR                | Missing not-at-random                               |
| MoCA                | MoCA, Montreal Cognitive Assessment                 |
| OTI-C               | Opiate Treatment Index – Criminality section        |
| OTI-I               | Opiate Treatment Index - Injecting drug use section |
| PHQ-15              | Patient Health Questionnaire-15                     |
| PPS                 | Per protocol set                                    |
| RAVLT               | Rey Auditory Verbal Learning Task                   |
| RCG                 | Readiness to Change Questionnaire                   |

|       |                                                     |
|-------|-----------------------------------------------------|
| RVIP  | Rapid Visual Information Processing                 |
| SAE   | Serious Adverse Event                               |
| SAP   | Statistical Analysis Plan                           |
| SDS   | Severity of Dependence Scale                        |
| SF-12 | Short Form-12 Health Survey                         |
| TEAE  | Treatment Emergent Adverse Events                   |
| TSQM  | Treatment Satisfaction Questionnaire for Medication |
| UDS   | Urine Drug Screen                                   |
| VAS   | Visual Analogue Scale                               |
| WTAR  | Wechsler Test of Adult Reading.                     |
| WURS  | Wender-Utah Rating Scale                            |

# **1. INTRODUCTION**

## **1.1. BACKGROUND**

Methamphetamine dependence is a growing public health concern. There is currently no pharmacotherapy approved for methamphetamine dependence. Lisdexamfetamine (LDX) dimesylate, used in the treatment of attention-deficit hyperactivity disorder and binge eating disorder, has potential as an agonist therapy for methamphetamine dependence, and possible benefits of reduced risk of aberrant use due to its novel formulation. We hypothesise that oral LDX treatment will result in significantly reduced methamphetamine use compared to placebo in people who are dependent on methamphetamine.

## **1.2. STUDY SYNOPSIS**

The LIMA trial [1] is a multi-center double blinded randomised controlled trial designed to evaluate the efficacy of 12 weeks of daily LDX 250mg in reducing methamphetamine use. The target sample is 180 adults with methamphetamine dependence of  $\geq 12$  months who report use of  $\geq 14$  days out of the previous 28. Eligible participants were randomised in a 1:1 ratio to a 15-week intervention consisting of either induction (1 week of 150 mg LDX), maintenance (12 week of 250mg LDX) and reduction (1 week of 50mg LDX, 1 week of 50mg LDX); or placebo. All participants were given access to four sessions of cognitive-behavioural therapy as treatment as usual and received a follow up visit 4 weeks post treatment (week 19).

## **2. STUDY OBJECTIVES**

LIMA is a randomised control trial designed with the primary objective to examine the efficacy of oral LDX in reducing methamphetamine use over a 12-week maintenance course of 250mg LDX daily comparing to placebo, and to examine the safety of oral LDX in people who are dependent on methamphetamine.

Secondary objectives are:

- To examine changes in physical and mental health, cognitive and psychosocial functioning and well-being in the study population between those taking oral LDX compared to placebo.
- To examine differences in retention rates in the study population between those taking oral LDX compared to placebo.
- To examine differences in amphetamine cravings, withdrawal and severity of dependence in the study population between those taking oral LDX compared to placebo.
- To examine differences in use of alcohol and other drugs in the study populations between those taking oral LDX compared to placebo.
- To examine differences in bloodborne virus transmission risk behaviour in the study population between those taking oral LDX compared to placebo.
- To examine difference in criminality in the study population between those taking oral LDX compared to placebo.
- To examine the abuse liability profile of oral LDX in people who are dependent on methamphetamine.

### **3. OVERALL STUDY DESIGN**

This study is a multicentre, double-blind, randomised placebo controlled, parallel design trial, comparing a 12-week maintenance course of 250mg LDX daily to placebo in the targeted 180 participants. Eligible participants were randomised in a 1:1 ratio to an intervention or placebo group.

#### **3.1. STUDY POPULATION**

The study population is treatment-seeking adults with long-standing ( $\geq 12$  months) methamphetamine dependence.

##### **3.1.1. Inclusion criteria**

1. Provide written, informed consent to participate in the study.
2. Aged 18 to 65 years.
3. Be treatment-seeking for methamphetamine use.
4. Meet ICD-10 criteria for methamphetamine dependence for at least twelve months.
5. Self-report methamphetamine use of  $\geq 14$  days out of the previous 28.
6. Have one urine drug screen (UDS) positive for methamphetamine at screening.
7. Be willing and able to comply with the requirements of the study.
8. The ability to store study medication securely.

##### **3.1.2. Exclusion criteria**

1. Current effective counselling-based treatment for methamphetamine dependence.
2. Current pharmacotherapy treatment for opioid dependence.
3. Use of prescription stimulant medication (e.g., dexamphetamine, modafinil, methylphenidate) in the previous four weeks (discuss with Trial Chairperson before excluding).
4. Current dependent use of alcohol or non-prescribed substances other than amphetamines, diagnosed by specialist clinical assessment against ICD-10 criteria, which in the opinion of the investigator would interfere with participation in the study.
5. Currently lactating or pregnant, or of childbearing potential and not willing to avoid becoming pregnant during the study.
6. Sensitivity or previous adverse reaction to LDX.
7. Current, severe medical disorder (e.g., cardiovascular disease, uncontrolled hypertension,

peripheral vascular disease, assessed by study medical officer).

8. Current, severe psychiatric disorder (e.g., acute psychosis, severe anxiety and/or mood disorder, intent to harm self or others assessed by study medical officer and/or psychiatrist).
9. History of glaucoma, hyperthyroidism, pheochromocytoma, motor tics, vocal tics, or Tourette's syndrome.
10. Use of monoamine oxidase inhibitors in previous 14 days, or use of other medications that could interact with study medication on assessment by the investigator.
11. Exposure to any investigational drug within the 4 weeks prior to screening
12. Not available for follow-up (e.g., likely travel or imprisonment).
13. Undergoing child protection service/court/work-ordered drug testing.

### **3.2. INTERVENTION**

Participants receive 250mg oral lisdexamfetamine/d over 12 weeks preceded by 7 days induction of 150mg/d and followed by a two week reduction period of 150mg/d for 7 days and 50mg/d for 7 days or identically matched placebo. All participants are offered 4 sessions of cognitive behavioural therapy (CBT) during the treatment period.

### **3.3. RANDOMISATION**

Participants will be randomised in a 1:1 ratio between groups, stratified by treatment site, using an independently computer-generated randomisation schedule. The randomisation schedule used blocks of size 4 and 6 with the size of block chosen at random and treatment allocations randomly permuted and balanced with blocks. The randomisation scheme was prepared using SAS 9.4.

### **3.4. BLINDING**

Participants, treating clinicians and study personnel are blinded to study treatment allocation. The active drug (LDX dimesylate) and the placebo were provided in identical capsules

Unblinding could occur during the conduct of the trial in emergency situations where management of an participant required knowledge of treatment allocation. In the event unblinding was required, the Principal Investigator would be contacted in all these instances but kept blinded to treatment allocation.

### **3.5. STUDY ENDPOINTS**

#### **3.5.1. Primary endpoint**

The primary endpoint is the change from baseline to week 13 in the self-reported number of days of methamphetamine use for the previous 28 days.

#### **3.5.2. Secondary endpoints**

The secondary endpoints are:

- total number of days of self-report MA use over the 12-week active treatment period (weeks 2–13);
- longest period of abstinence during the treatment period;
- percentage of participants achieving  $\geq 21$  consecutive days abstinence during the treatment period;
- number of MA negative UDS in the 4 weeks prior to week 13 (Treatment Effectiveness Score [2], with missing UDS assigned as positive);
- retention rate at weeks 5, 9, 13 and 19;
- measures of amphetamine craving, withdrawal, and severity of dependence:
  - Visual Analogue Scale for cravings (VAS),
  - Amphetamine withdrawal questionnaire (AWQ),
  - Severity of Dependence Scale (SDS);
- measures of abuse liability, other drug use, risk behaviour and crime:
  - Drug Evaluation Questionnaire-5 (DEQ-5),
  - Timeline follow back (all drugs—past 28 days),
  - Urine drug screen (UDS),
  - Opiate Treatment Index-Injecting Practices (OTI-I),
  - Blood borne virus transmission risk behaviour measured by days of injecting,
  - OTI-Crime (OTI-C),
  - Substance Use and Sex Index (SUSI);
- measures of physical and mental health and cognitive and psychosocial functioning:
  - Patient Health Questionnaire-15 (PHQ-15),
  - Short Form-12 Health Survey (SF-12),

- Brief Psychiatric Rating Scale (BPRS-4),
- Depression & Anxiety Survey Scale (DASS-21),
- WHO Quality of Life-BREF,
- Insomnia Severity Index (ISI);
- treatment satisfaction, measured by Treatment Satisfaction Questionnaire for Medication (TSQM);
- medication adherence:
  - supervised doses,
  - take away dispenses;
- testing the blind.

### **3.5.3. Safety endpoint**

The safety endpoints are:

- all AEs and that are possibly or probably treatment related, that occur during the study treatment period or within 30 days of the last dose of study treatment;
- all serious adverse events (SAEs);
- discontinuations due to Treatment Emergent Adverse Events (TEAEs);
- suspected unexpected serious adverse reactions (SUSARs).

## **3.6. SAMPLE SIZE**

Based on the primary outcome measure (days of methamphetamine use out of 28 days), to detect a mean difference of 4.5 days (9 days in control vs. 4.5 days in the LDX group out of 28 days) at week 13 (12 weeks post treatment), assuming a pooled standard deviation (SD) of 9 days (i.e. median effect size  $d=0.5$ ), with over 80% power at a two-sided significance level of 0.05, a sample size of 126 (63 per group) is required. Taking into account an estimated attrition rate of 30%, 180 participants in total (90 per group) need to be randomised.

Prior to unblinding, the observed pooled standard deviation, achieved sample size and attrition rate will be used to recalculate the power of the study to detect the same effect size.

### **3.7. INDEPENDENT DATA SAFETY MONITORING COMMITTEE (IDSMC)**

The IDSMC monitored recruitment and the data related to outcomes and safety at least annually during conduct of the study. The IDSMC was scheduled to review unblinded data to examine participant characteristics, treatment compliance, outcomes and adverse events, when the 50th participant completed treatment or 6 months after the commencement of recruitment, whichever occurred first, with subsequent meetings in accordance with the IDSMC charter. The DSMB could recommend stopping the trial if the number and/or severity of adverse events justified discontinuation of the study; or on the basis of a positive efficacy result only when the primary endpoint (methamphetamine use) data are truly compelling and the risk of a false positive conclusion was acceptably low ( $p < 0.001$  for primary endpoint). The DSMB met on the 30th May 2019, 12th February 2020, and 7th October 2021, and recommended continuation of the trial each time.

### **3.8. DATA COLLECTION AND SECURITY**

This study uses electronic data capture in the form of REDCap (Research Electronic Data Capture). The REDCap database is located on a standalone database server hosted by Hunter New England Local Health District (HNELHD). Backup systems and firewalls are in place. Access to the system is restricted to authorised personnel and password protected.

All data entered into REDCap have supporting identifiable source documentation, which are held confidentially in line with current legislation governing health information, and destroyed 15 years after study completion.

## **4. STATISTICAL METHODS**

### **4.1. GENERAL CONSIDERATIONS**

#### **4.1.1. Analysis principles**

Summaries of continuous variables will be presented as means and standard deviations, or as medians and interquartile ranges, as appropriate. Categorical variables will be presented as frequencies and percentages.

For comparisons between the two randomised groups, the estimand of interest is the expected difference in outcomes between the prescribed course of LDX and usual care, among participants who receive at least one dose. This corresponds to a modified intention-to-treat (ITT) approach to the analyses, whereby all randomised participants who received at least one dose of the prescribed medication are included according to their allocated arm. That is, withdrawal prior to receiving the first dose will be handled using a principal stratum strategy, on-study death will be handled using a hypothetical strategy, and all other intercurrent events will be handled using a treatment policy strategy.

For each outcome variable, statistical significance will be assessed at the 0.05 level using a two-sided test. In addition to treatment effect estimates and p-values, 95% confidence intervals will be reported to describe uncertainty about the effect of treatment.

No adjustment for multiple testing is planned, as the primary comparison is at a single predefined time point (week 13). However, all results will be reported and interpreted by considering both the strength of the evidence and the consistency of effects across endpoints.

All analyses will be performed using SAS version 9.3 or later, and R 4.0 or later.

#### **4.1.2. Analysis dataset**

The primary and secondary outcomes will be analysed on the full analysis set following the modified ITT principle described above; that is, by including all randomised participants who received at least one dose of the prescribed medication according to the group to which they were randomised and regardless of protocol compliance.

#### **4.1.3. Missing data handling**

The patterns of missing data over time and between groups will be summarised in tables and graphs. Reasons for missingness will be described and explored. Logistic regression will be used to explore the potential factors related to missingness and withdrawal. The handling of missing data will follow the National Research Council (US) Panel recommendations on Handling Missing Data in Clinical Trials [3], as described below and in Section 4.3.

For longitudinal analyses, the likelihood-based mixed model for repeated measures (MMRM) approach will be utilised, which depends on a missing at random (MAR) assumption [4]. The MMRM approach makes use of all available data and is reliable for effect and standard error estimates under the MAR assumption.

Sensitivity analyses will be performed to assess the robustness of the main results to different missing data assumptions [3] [5]. Details can be found in Section 4.3.3.1.

### **4.2. SUMMARY OF STUDY DATA**

#### **4.2.1. Protocol deviations**

Protocol deviations will be summarised as the number of deviations by type (randomisation of an ineligible participant, failure to comply with study treatment, and other). All protocol deviations will be listed with a description of the deviation and the corrective action taken.

#### **4.2.2. Participant disposition**

All subjects who were invited to participate in this trial will be accounted for, and a CONSORT flow chart will be prepared. Reasons for early withdrawal will be listed for all participants that prematurely withdrew from the study. The number of participants that were screened but not randomised will be presented and the reasons for their non-participation will be listed (where available).

#### **4.2.3. Participant characteristics**

Baseline demographic variables such as age and gender, and relevant clinical variables will be summarised for each treatment group.

#### **4.2.4. Concomitant therapy**

Concomitant medications will be categorised based on the WHO Anatomical Therapeutic Chemical classification system. The frequencies and percentages of participants taking concomitant medications before and after randomisation will be summarised by treatment group.

#### **4.2.5. Treatment adherence**

Medication adherence is assessed daily for days 1–5 of week 1 and weekly thereafter. The number of CBT sessions attended (out of a total possible of four) will be recorded. These will be summarised by treatment group.

### **4.3. ANALYSIS OF PRIMARY OUTCOME**

#### **4.3.1. Analysis method**

The primary outcome is the number of days of self-reported methamphetamine use in the past 28 days. The primary efficacy measure is the difference between the two groups in the change in the number of days of methamphetamine use from baseline to week 13.

A likelihood-based mixed effects regression model approach will be used for the primary efficacy analysis. The days of methamphetamine use at baseline and all post-baseline assessments (weeks 5, 9, 13 and 19) will be the time-varying dependent variable. Covariates will include (categorical) visit, randomised treatment group, and their interaction, with the coefficient corresponding to the difference between groups in the change from baseline to week 13 being the parameter of primary interest. Site will also be included as a covariate in order to account for its use in the stratification of the randomisation. Participant-specific random effects will be included in order to account for temporal correlation in the outcome measure.

The initial model will assume a multivariate normal distribution. However, if residual-based model checks suggest that this is inappropriate (e.g., due to heteroscedasticity), a generalised linear mixed effect models will be considered: a binomial or double binomial (in the case of evidence of under- or overdispersion) outcome distribution may be more appropriate.

#### **4.3.2. Supplementing missing TLFB28 data with available TLFB7 data**

The number of days of MA use in the past 28 days at baseline and weeks 5, 9, 13 and 19 was collected

during the study period using the 28-day timeline follow back (TLFB28) approach. At weekly visits during the study period up until week 13, the number of days of MA use in the past 7 days was also collected using the 7-day timeline follow back (TLFB7) approach.

The primary outcome measure will be based on the data collected using the TLFB28 approach. As described in Section 4.1.3, the primary analysis method (mixed effects regression) allows for missing outcome data and is valid under a missing at random (MAR) assumption. However, it is possible that there will be some 28-day periods for which the full TLFB28 outcome is missing but some TLFB7 data, covering part of that period, are available. As such, this Section describes how the available TLFB7 data will be used to supplement the missing TLFB28 data.

If at least one TLFB7 measure is available but the full 28-day outcome is not calculable and otherwise not available for a given 28-day period (i.e., the remaining TLFB7 measures are missing, along with the TLFB28 measure), multiple imputation will be employed to produce imputed 28-day outcomes based on the observed data. Specifically, imputed values for the missing TLFB7 measures will be produced using predictive mean matching based on the observed TLFB7 and TLFB28 measures, and the missing TLFB28 measures will passively imputed [6] by adding together the observed and imputed TLFB7 measures for the given 28-day period. Where a TLFB28 measure is missing and no TLFB7 measures are available for the corresponding 28-day period, the primary outcome will be left as missing.

The primary analysis method (mixed effects regression) will be applied to the imputed datasets, and the results combined according to Rubin's rules [7]. This approach allows us to use the collected 7-day measures to inform the analysis of the 28-day outcomes where they would otherwise be missing, and appropriately account for the uncertainty in doing so.

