### **4.3.3. Supportive and sensitivity analyses**

#### **4.3.3.1. Sensitivity to missing data assumptions**

As described in Sections 4.3.1 and 4.3.2, the primary analysis will use available TLFB28 data and imputed TLFB28 data for the 28-day periods where some TLFB7 data are available. This analysis is valid under a missing at random (MAR) assumption, conditional on variables included in the imputation and regression models [8]. Given the possibility of substantial missingness in the primary outcome, sensitivity analyses will be carried out to examine the robustness of the estimate from the main analysis to departures from its assumptions.

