### **(1) sensitivity analysis assuming missing at random (MAR)**

Multiple imputation by chained equation (MICE) will be performed to produce 100 complete imputed datasets [9] [10]. Variables in the MI model will include the primary outcome at baseline and weeks 5, 9, 13 and 19, covariates from the analysis model, covariates associated with discontinuation, as well as other variables and measures in the collected data.

Each imputed dataset will be analysed using the same mixed effects regression model as used for the primary analysis. The results from the imputed datasets will be pooled to form a single inference following Rubin's rules [7].

Given that the primary analysis treats the baseline outcome as a dependent variable, a second sensitivity analysis of the imputed data will be undertaken in which the baseline outcome is included as a fixed covariate, and only the post-baseline outcomes treated as dependent variables. This will evaluate the impact of the assumption in the primary analysis that the conditional distribution of the baseline outcome is the same as that of the post-baseline outcomes, which may be questionable due to the inclusion criterion that is based on the baseline days of methamphetamine use.

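### The imputation feeding the primary analysis does not name randomised arm or site as predictors, so the week 13 effect can be biased in partly observed windows

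*SAP*

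**What the plan says.** SAP 4.3.2 deals with 28-day windows in which the 28-day timeline follow-back (TLFB28) is missing but at least one weekly measure (TLFB7) exists. For these, "imputed values for the missing TLFB7 measures will be produced using predictive mean matching based on the observed TLFB7 and TLFB28 measures", and the 28-day total is then formed "by adding together the observed and imputed TLFB7 measures for the given 28-day period". Windows with no weekly data are not touched: where "no TLFB7 measures are available for the corresponding 28-day period, the primary outcome will be left as missing". Weekly data were collected "At weekly visits during the study period up until week 13", so the week 19 window cannot be filled this way.

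This step belongs to the primary analysis and is not a sensitivity analysis: "The primary analysis method (mixed effects regression) will be applied to the imputed datasets", with pooling by Rubin's rules. The model it feeds is set out in SAP 4.3.1: "Covariates will include (categorical) visit, randomised treatment group, and their interaction", plus site.

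Two other statements bear on the point. The separate missing-at-random (MAR) sensitivity imputation in SAP 4.3.3.1 lists among its variables "covariates from the analysis model, covariates associated with discontinuation", and fixes 100 imputed datasets. The opening of 4.3.3.1 says that the primary analysis is "valid under a missing at random (MAR) assumption, conditional on variables included in the imputation and regression models". Section 4.3.2 itself names neither arm nor site and gives no number of imputations.

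**The concern.** The parameter of interest is the difference between arms in change to week 13. An imputation model that lacks arm draws a participant's missing weeks from donors in both arms, matched only on observed use. Those draws are right only if arm tells us nothing further about the missing weeks once the observed weeks are known. The SAP does not state that assumption, and it is stronger than MAR given arm and observed use. Having arm in the regression model fitted afterwards does not correct values already drawn without it.

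At stake is a bias in the primary estimate that more participants would not remove. Part of any gap between the primary result and the MAR sensitivity result could also come from the different imputation variables.

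**Working it through.** **1. The plan's own figure.** Inputs from SAP 3.6: difference 4.5 days, SD 9, two-sided 0.05, 80% power, 30% attrition. n per arm = 2 × (1.96 + 0.84)² × 9² / 4.5² ≈ 62.8, so 63 per arm and 126 in total; 126 / 0.70 = 180. This reproduces. Power at 63 per arm is 80.1% by the normal approximation (79.5% by the t-test), so there is no slack.

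**2. Closed form, constant effect.** Assumptions not in the SAP: equal correlation ρ between weeks, the same effect every week, k observed weeks as the only predictors, and a share f of participants with a partly observed week 13 window.
- A missing week imputed without arm keeps R = kρ / (1 + (k − 1)ρ) of its effect.
- A window with m observed weeks keeps W = (m + (4 − m)R) / 4.
- The overall effect is 4.5 × (1 − f(1 − W)).

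With one observed week in the window (m = 1) and f = 20%:
- That week as the only predictor (k = 1), ρ = 0.5: R = 0.50, W = 0.625, effect 4.5 × (1 − 0.2 × 0.375) = 4.16 days, a 7.5% loss. At ρ = 0.7: W = 0.775, effect 4.30 days, a 4.5% loss.
- Adding the eight earlier treatment weeks (k = 9), ρ = 0.5: R = 4.5 / 5 = 0.90, W = 0.925, effect 4.43 days, a 1.5% loss. At ρ = 0.7: R = 0.955, W = 0.966, effect 4.47 days, a 0.7% loss.

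Section 4.3.2 does not confine predictors to the window, so k = 9 is the fairer reading. Over ρ from 0.3 to 0.8, f up to 30% and 9 to 11 observed weeks, the effect stays between 4.29 and 4.50 days.

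**3. Simulation, other effect shapes.** Settings: 180 participants, 12 weekly counts limited to 0–7, baseline and all earlier weeks as predictors, one to three weeks of the week 13 window observed and the rest missing completely at random, predictive mean matching, 5 imputations, 300 runs. The contrast is the week 13 difference in means, not the full mixed model. Limiting the counts to 0–7 makes the full-data effects smaller than 4.5. Results in days at f = 30%:

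| Effect over the 12 weeks | ρ | Full data | Without arm | With arm | Shift without arm |
|---|---|---|---|---|---|
| Constant | 0.4 | −3.08 | −2.97 | −3.07 | 0.11 towards zero |
| Constant | 0.7 | −3.33 | −3.28 | −3.32 | 0.05 towards zero |
| Growing | 0.4 | −3.45 | −3.09 | −3.40 | 0.36 towards zero |
| Growing | 0.7 | −3.78 | −3.47 | −3.71 | 0.31 towards zero |
| Late onset | 0.4 | −3.04 | −2.67 | −3.00 | 0.37 towards zero |
| Late onset | 0.7 | −3.10 | −2.75 | −3.05 | 0.35 towards zero |
| Waning | 0.4 | −1.67 | −1.94 | −1.69 | 0.27 away from zero |
| Waning | 0.7 | −1.91 | −2.26 | −1.96 | 0.35 away from zero |

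At f = 10% the shifts without arm were 0.01 to 0.13 days. With arm in the imputation model, every scenario was within 0.07 days of full data. A harder constant-effect run (continuous values, exactly one week observed, ρ = 0.5, f = 30%) gave −4.49 with full data, −4.34 without arm and −4.49 with arm, a shift of 0.15.

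**4. Meaning for power.** Holding SD 9 and 63 per arm, power is 78.3% at 4.4 days, 76.5% at 4.3 and 74.5% at 4.2, against 80.1% at 4.5.

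**The case against.** Four objections have force.

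- **Silence is not exclusion.** A reader might infer that the SAP deliberately leaves arm out. It does not say so; it simply does not name arm. Even so, 4.3.2 sets out to specify the basis of the imputation, and the sensitivity imputation in 4.3.3.1 does list the analysis covariates. A programmer following 4.3.2 to the letter would omit arm.
- **The direction is not fixed.** A reader might infer that the effect is always pulled towards zero and that the omission is at worst conservative. The waning-effect rows show the opposite. The earlier weeks then carry a larger effect than the missing ones, and the draws inherit it.
- **The size is often small.** A reader who takes one observed week as the only predictor would arrive at losses of 4.5% to 7.5% at a 20% share. Once earlier weeks are used, as 4.3.2 allows, a constant effect loses about 0.7% to 1.5%. Partial windows may also be few. A participant who gives the 28-day recall at week 13 supplies the whole window even after missed weekly visits, and windows without weekly data are left missing.
- **The two MAR analyses differ in other ways.** A reader might put any gap between them down to arm alone. The sensitivity imputation also completes all missing outcomes and adds predictors of discontinuation and other measures, so arm is one difference among several.

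All four limit the direction, size or attribution of the bias. None supplies the missing term, and the sensitivity analysis could reveal the problem without repairing the primary estimate.

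**Conclusion.** The point stands as a specification defect in the primary analysis. As written, the imputation model is narrower than the model it feeds, in the very term being estimated. The validity claim in 4.3.3.1 then needs arm to add nothing given observed use, which the SAP does not state.

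The bias is usually towards zero, and away from zero if the effect fades within the window. With a constant effect and earlier weeks as predictors it is about 0.1 days or less in the main simulations. With a growing or late-onset effect and an assumed 30% share of partial windows it reaches about 0.37 days, roughly 12% of the simulated effect (0.37 / 3.04). The share of partial windows, the between-week correlation and the course of the effect over time are all assumptions. The simulation used a week 13 difference in means in place of the mixed model. It is worth correcting because the remedy is nearly free and the primary estimate is affected.

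**What to change.** Amend SAP 4.3.2 so that the predictive mean matching uses randomised treatment group and site together with the observed weekly and 28-day measures at all visits, and state 100 imputations, as in 4.3.3.1. The cost is one sentence and little computing.

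Imputing separately by arm is an acceptable alternative but is not required, since including arm brought the simulated effect back to within 0.07 days of full data. It shrinks the donor pools: 90 are randomised per arm, or about 63 with data if the planned 30% attrition applies (0.7 × 90).

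The amendment table records a change approved after unblinding, so the primary analysis may already have been run. If so, record which imputation variables were used. If arm was omitted, report the arm-inclusive result alongside. Give the number of partly observed windows per arm at each visit, so that a reader can judge how much the step matters.
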